### Consent process

During screening, participants will give informed written consent to their data being used for clinical cohort and HE study (consented together prior to allocation to HE study) and the modelling (Phase 2). In cases where prospective consent not possible, deferred consent model will be offered (to allow those who initially lack capacity to be represented in the cohort. A separate written consent will be sought for the participants recruited to the situation analysis including health care workers.

We will obtain informed consent from patients if their physical and mental capacity allows based on the following questions: 1) can the patient retain information; 2) can the patient weigh the information; 3) can the patient communicate a decision. Where there is uncertainty, these can be assessed through: 1) asking the patient to reflect the given information back to the study staff, including the purpose, procedures and risks of the study; 2) asking the patient to convey the alternatives of participation in the study, including understanding the voluntary nature of inclusion.

For fully competent patients, an information sheet will be provided, the study will be discussed and written consent obtained. Illiterate patients will be read the information sheet and mark the consent form with either a cross or thumbprint to indicate their agreement in the presence of an independent witness. If a patient is unable to give consent, we will obtain consent from a proxy (a relative or representative) in the same manner. Where the patient subsequently regains capacity, we will approach them to discuss and obtain retrospective consent. If no proxy is available and local regulations allow, we will use a deferred consent process. If deferred consent is used, we will tell the patient about the study as soon as possible and obtained consent for use of the data collected. If the patient does not have capacity or if a significant delay to regaining capacity (>7 days) is anticipated, then we will seek retrospective assent from their proxy.

Justification for this consent model is that patients stand to benefit from early use of enhanced diagnostics using CE marked and commercially available point of care tests. Delayed diagnosis in this context has potentially detrimental effects for patients who otherwise would not have access to the enhanced diagnostic package. Patients will be at minimal risk through study procedures. From a scientific perspective, this model will reduce the risk of recruitment bias. There is precedence for deferred consent in the Malawian context with existing data describing the acceptability of this approach
^
26
^. Deferred consent has also been used in Tanzania for a randomised controlled trial of tranexamic acid
*versus* placebo after post-partum haemorrhage
^
27
^. All participant information sheets and consent forms will be translated into local languages (kiSwahili in Tanzania, and Chichewa in Malawi).

### Variables

**
*Phase 1 A: Prospective longitudinal cohort study*.** The main outcome is to define the characteristics of multimorbidity. We will employ enhanced point of care test (POC) diagnostics for patients admitted to the study to determine the prevalence of multimorbid diseases of interest (specifically HIV, hypertension, diabetes and chronic kidney disease). All POCs used in the study are CE marked and commercially available. We will make the results of these tests available to treating healthcare providers using a standardised proforma. No treatment recommendation will be provided with this information and clinicians will be able to interpret and use this information independently. Structured data extraction of clinical information (including potential predictors of patient outcomes) will be performed at intervals (described in
Table 1 from patient records.

**
*Phase 1 B: Health economic evaluation*.** To explore the impact of socioeconomic status (SES) on patient costs, clinical outcomes and health-related quality of life (HRQoL) we will calculate wealth scores and use these to assign all clinical cohort study participants to SES quintiles. For participants randomised to the health economic study, we will collect data on patient costs at admission (in person), discharge (in person), 30 and 90 days post discharge (in person or by telephone). Health system costs for patients in the cohort study will be modelled using top down and bottom up costing methods. HRQoL will be estimated in quality adjusted life years (QALYs).

**
*Phase 1 C: Situation analysis*
** In depth interviews (IDI) and focus group discussions (FGD) with patients recruited to the cohort study, and their care givers will be conducted to understand their experiences, preferences, and priorities, including level of health literacy and engagement with healthcare providers for long term management of chronic conditions. Exploration of detailed experiences from patients and carers will provide specific concrete examples of their expectations, and any concerns they have, as well as their priorities and perceptions of how the hospital currently manages acute medical patients with multimorbidity, problems and how best to address them.

In-depth interviews and structured discussions with health care providers who provided direct care for patients recruited in the cohort study will be conducted to determine “nodes” in the treatment pathway where an intervention could effectively be delivered. Key informant interviews with policymakers at national and district level will explore the pathways of health care for people living with multimorbidity, their perspectives of the policy environment around the management of multimorbidity, and how an intervention could be incorporated into current practice.

Observations of patient care pathways in a purposefully selected sample of participants, will describe the patient pathway, and the effect of hospital context on acute medical care for multimorbid disease. We will observe the functioning of the wards, the relationship among healthcare workers (HCWs) and between HCWs and the patients. We will conduct semi-structured observation of hospital activities, patient pathways and patient consultations for adults admitted with acute medical conditions.

### Data sources and measurement

**
*Phase 1 A: Prospective longitudinal cohort study - baseline and clinical data*.** The primary outcome of the clinical cohort study will be to collect data on conditions known to be highly prevalent among medical in-patients in sSA, and are likely to be disease constituents of multimorbidity. Following results from a recent systematic review
^
24
^, we will therefore focus on HIV, hypertension, diabetes and chronic kidney disease. Importantly these conditions can be diagnosed using available point-of-care tools. Although heart failure is also a common in these settings, diagnosis is technically more challenging and is being explored separately. We will apply standardised point of care testing to participants and record these primary outcome conditions both in the electronic data capture tools and in the patient notes, making these explicitly available to treating clinical teams.

HIV: HIV will be tested using locally available HIV rapid diagnostics tests. For HIV positive patients we will also test the HIV viral load using existing laboratory infrastructure in each site.

Hypertension: In patients with a regular pulse rhythm, automated electronic sphygmomanometer will be used. In patients with an irregular pulse rhythm, manual aneroid sphygmomanometer will be used. Patients will be semi-recumbent or supine, legs uncrossed, relaxed for at least five minutes after the start of the consultation, and not talking. On the first visit, the blood pressure will be taken from both arms and using the arm with the highest reading thereafter. At each visit two readings will be taken from this arm, recording the second reading.

Diabetes: HbA1c levels will be measured using the POC Hemocue
^®^ HbA1c 501 Analyzer and cartridges (HemoCue AB, Ängelholm, Sweden).

CKD: Abbott iSTAT point-of-care device (Abbott Point of Care Inc, Illinois, USA) with Chem8+ cartridges will be used to measure creatinine from venous blood, directly following the manufacturer’s iSTAT User Guide.

Other conditions are expected to contribute to multimorbidity, for example hearing and visual impairment, causes of impaired mobility such as injury at birth, or disability from trauma, surgical procedures and others later in life. A key criterion for inclusion in the planned intervention study will be potential for improved morbidity or mortality from linkage to care. We will therefore collect data on disability using standardised questionnaires, with key components from Washington Group on functioning, Patient Health Questionnaire (PHQ)-9 for depression in addition to data tools used in previous cohort studies for the collection of standardised clinical information, and allow this to inform the intervention design.

Clinical outcomes, coded from a structured case summary and the available medical notes, will be established as follows:

1.Medical diagnosis and supporting evidence.2.In-patient treatment of these diagnoses, including time of appropriate treatment establishment.3.Vital signs, including pulse oximetry (using a A310 finger oximeter), respiratory rate, pulse rate, blood pressure and temperature.4.Routine laboratory data supporting these diagnoses (such as urine lipoarabinomannan [LAM], serum CrAg).5.Clinical outcomes will also be ascertained at hospital discharge, 30 days and 90 days as:6.Death (coded from all available records).7.Readmission to hospital.

Data will be collected by a study nurse using electronic data capture. This will describe the patient characteristics, medical history and ‘patient journey’ through the healthcare system. Age, date of birth and sex will be documented from patient reports and/or clinical notes. To ensure complete data collection, we will prospectively collect data on vital signs, details of resuscitation, medication administration, results of clinical, laboratory, and radiologic examinations. All clinically relevant findings will be entered into the medical notes to ensure availability to the responsible clinicians.

As a component of the functional assessment, we will measure hand grip strength at day 90 follow-up using a GRIPX Digital Hand Dynamometer, which is a known predictor of health and overall strength
^
28
^. Grip strength will be measured seated on a chair without elbow rests, with the elbow loosely flexed at 90
^0^, and the wrist in a neutral position
^
29,
30
^. Grip strength will be measured as the mean of three tests on both hands with 60 seconds of recovery between each attempt.

**
*Phase 1 B: Health economic data sources and measurement*.** All consenting study participants will be asked asset ownership, house construction and demographic questions extracted from the most recent relevant national Demographic and Health Survey (DHS). Patient cost data will be captured before, during, and for 90 days after hospital admission using an amended version of the STOP-TB tool, a widely-used questionnaire for measuring TB patient costs
^
31
^. We will capture direct medical costs (
*e.g.*, drugs, diagnostics, consultation and inpatient fees), non-medical costs (
*e.g.*, food and transport), indirect costs (lost time for patients and guardians). Where a patient is readmitted to hospital, we will also capture these costs. Costs will be captured in local currency and presented in 2024 United States dollars.

Health system costs will be collected using top-down and bottom-up (micro) costing methods. We will develop and validate (with relevant hospital staff) a visual model of individual patient pathways through the study hospitals. This will be supplemented with data on waiting times, and time spent with various health workers from the sample of patients that are included in observations conducted as part of the situation analysis. Costs for each stage of the patient pathway (triage, admission, diagnostics, treatment, discharge, readmission
*etc*.) will be based on unit costs for tests, staff time, hospital bed days and other inputs, obtained from hospital data, tests and consumables suppliers, and Ministry of Health (MoH). Any other costs deemed relevant during the data collection stage will also be included. Top-down costing data on hospital overheads (utilities, building costs, maintenance,
*etc*.) will be obtained for each hospital.

HRQoL data will be collected using the EQ-5D-5L questionnaire in English, Chichewa (Malawi) and kiSwahili (Tanzania). The questionnaire will be administered, at admission, discharge, 30 and 90 days post admission in person or (day 30) by phone (as for patient costs).

**
*Phase 1 C: Situation analysis*.** Experienced social science fieldworkers fluent in the predominant local language (kiSwahili in Tanzania and Chichewa in Malawi) will collect data with guidance from the clinical academic teams. Observation tools and interview topic guides will be piloted to ensure understandability, and promote effective dialogue and data generation. We will conduct one pilot observation and interview for each of the patient, caregivers and HCW groups. After this, early observation notes and interview transcriptions will be reviewed by the senior academic team to verify and refine as required the phrasing of questions and level of probing. Interviews and focus group discussions will be audio-recorded. During focus group discussions, a note-taker will assist the facilitator and record differences and similarities among group members in their reaction and response to questions. These steps will promote diversity in data collection.

### Sample size

**
*Phase 1 A: Prospective longitudinal cohort study*.** The primary outcome will be disease prevalence. At 5% prevalence, a precision of 1.5% and power of 90% at α=0.05 is expected (precision will reduce as actual estimate rises towards 50%). We will use 5% prevalence as the lower boundary for inclusion of the disease during intervention development. We expect that HIV, hypertension and diabetes will meet this threshold. The cohort will allow us confidence to decide on the inclusion of chronic kidney disease. Prevalence will be assessed in both countries at the district and central hospital level to determine if findings are shared across settings. Given these assumptions, sample size is 1544 patients, with a target of 1600 to account for drop out. We will recruit these patients across the four hospitals (with numbers varying between sites due to different patient loads).

**
*Phase 1 B: Health economic evaluation*.** A randomised sub-sample of one third of the cohort study participants will be selected for participation in patient costing and HRQoL analysis (approximately 133 participants per hospital).

**
*Phase 1 C: Situation analysis*.** Sampling strategies for patients and caregivers is designed to include those individuals representing: those admitted for the first time and those who are returnees; those on HDU, ICU and ordinary wards; different age categories; male and female. We will ensure inclusion of patients with multiple known pathologies representing “multimorbidity” according to the final definition. Sample sizes for interviews are preliminary; they will continue until a point of saturation is reached.
Table 2 shows estimates of the number of patient and carer interviews required. For healthcare workers, we will include different cadres working in different departments.

**Table 2. T2:** Number of in-depth interviews, focus group discussions and structured discussions.

PER HOSPITAL SITE	In-depth interviews	Focussed group discussions	Structured discussions
Patients with multimorbidity *	10	24	10
Caregivers to patients with multimorbidity *	10	24	10
Doctors	2	-	4
Nurses	4	-	8
Ward attendants	2	-	6
Reception / frontline administration staff	2	-	2
Total	30	48	40

* Patients and caregivers will not be the same group during IDIs and FGDs. IDI, In depth interviews; FGD, focus group discussion.

Observations will be conducted at different days of the week and at different times of the day including both the morning and afternoon hours (examining variation over time). In each day, the observer will spend four to five hours conducting these hospital observations with a further two to three hours of reflection to document and expand the observation notes. We will observe 40 patients consultations (10 patients per hospital), including a sequence of observations throughout their follow-up to establish pathways, timings and bottlenecks in the system. Observers will balance male and female patients, observing different consultation rooms and patients admitted at different times of day.

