AE: adverse event; POC: point of care blood test; HIV: human immunodeficiency virus; VL: viral load; urine LAM: urinary lipoarabinomannan; CrAg: cryptococcal antigen; HbA1c: haemoglobin A1c (glycated haemoglobin). Additional contact with the participants may be made up to approximately 12 months after hospital admission to check the longer-term outcomes. This will be by telephone where possible. Visit F (hospital discharge) visit data will be collected, this may occur at any point before or after the 2, 5 and 7 day follow up visits. Visit G (90 day) will occur in a specific research outpatient follow-up clinic. There will be flexibility of ±10 working days for this follow up visit to take place. * Diagnostic HIV test and/or HIV viral load will be collected as part of routine clinical service. Parentheses indicate only if required to confirm diagnosis (rely on concurrent or earlier test). 1: Samples for urinary LAM and serum CrAg test will be collected and processed as part of routine clinical service to screen for opportunistic infection in line with WHO guidance at admission. 2: Qualitative interviews will take place with healthcare workers in a portion of treating providers after patient discharge. Qualitative interviews will take place with a proportion of patients after follow up visit at 90 days. 3: Written consent will be taken at the earliest possible opportunity, either directly from the patient or from a proxy (if patient lacks capacity). 4: Telephone or home visit follow-up (in order to maximise retention and data completeness)

**
*Phase 1 B: Health economic evaluation*.** One third of participants recruited to the cohort study will be randomised to the health economics study, with follow-up and data collection as per cohort study, or as detailed in section (Variables, below).

**

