## Limitations

There are a number of limitations with this study, which we have attempted to mitigate. First, there are a limited number of sites in two countries. In order to generate broadly generalisable results, the chosen sites reflect a mix of tertiary / referral hospitals and district hospitals in each country. Second, we have decided to systematically screen for four conditions (HIV, hypertension, diabetes and CKD) using point-of-care diagnostics. This may miss multimorbidity from other chronic conditions, which require additional infrastructure to confirm diagnoses (such as clinical imaging or enhanced laboratories), but we will collect clinical data on all diagnosed chronic conditions. A recent systematic review indicates a high burden of disease from these four conditions among hospitals patients, which can importantly be diagnosed using available point-of-care tools
^
24
^. Third, CKD diagnoses require evidence of chronicity of disease at three months and therefore data in this condition is prone to survivorship bias. Fourth, EQ5D-5L data and resulting QALY estimates may not reflect the most accurate picture of HRQoL in our study context. However, through our eCRF, we will collect rich clinical data with additional scales (such as the Patient Health Questionnaire-9 [PHQ-9] screening tool for depression
^
34
^; and clinical frailty scale
^
35
^ to explore the possible limitations and interrelationships. Fifth, our planned situation analysis will provide a cross-sectional picture of the health system at the time of the study, which is not able to incorporate the dynamic and adaptive nature of health systems. However, the MultiLink consortium includes researchers from each country and site, with a rich understanding of the context.

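### The stated confidence and 90% power for deciding on CKD do not follow from a sample size with a 3.5% loss allowance, because new CKD can be confirmed only at the day-90 clinic visit

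*Protocol article*

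**What the plan says.** All references are to the protocol article.

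- **Sample size, Phase 1 A.** The design statement is "At 5% prevalence, a precision of 1.5% and power of 90% at α=0.05 is expected". The decision rule is "We will use 5% prevalence as the lower boundary for inclusion of the disease during intervention development". HIV, hypertension and diabetes are expected to pass, which leaves CKD as the open question: "The cohort will allow us confidence to decide on the inclusion of chronic kidney disease". The number is given once for all conditions: "sample size is 1544 patients, with a target of 1600 to account for drop out".
- **Table 1 and its footnotes (Participants).** Study creatinine is scheduled at day 0 and day 90 and at no visit between. On the second of these, "Visit G (90 day) will occur in a specific research outpatient follow-up clinic", and "There will be flexibility of ±10 working days for this follow up visit to take place".
- **Limitations.** "CKD diagnoses require evidence of chronicity of disease at three months and therefore data in this condition is prone to survivorship bias". The section opens by saying that mitigation was attempted. A response follows the first, second, fourth and fifth limitations, but not this one.
- **Analysis, Phase 1 A.** Multiple imputation by chained equations is planned where appropriate. The text does not link it to CKD status, to deaths before day 90 or to the denominator of the CKD prevalence.
- **Introduction.** An earlier review is cited for a CKD prevalence of 7.7% among medical inpatients, with poor data on chronicity.

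**The concern.** HIV, blood pressure and HbA1c are measured at admission, so nearly every enrolled patient can contribute to those prevalences. CKD differs because a raised creatinine at admission does not separate chronic from acute disease. By the article's own account the distinction needs evidence at three months. A patient who dies or does not attend has no confirmatory study test.

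Two separate problems follow. The first is information: an allowance of 3.5% may fit conditions measured on day 0, but it is also applied to a condition that depends on survival and attendance to day 90. The second is bias: if patients with CKD are more likely to die or miss the visit, which is plausible but not documented here, the CKD prevalence is underestimated. A larger sample would not cure the second problem.

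What is at stake is the one inclusion decision that the cohort is said to settle. CKD is also one of the four conditions used to describe multimorbidity. The cited 7.7% lies near enough to 5% for moderate bias to matter.

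**Working it through.** **1. The plan's own figures.** Inputs from Sample size: prevalence 5%, difference 1.5 points, power 90%, α = 0.05 (sidedness not stated). A one-sided one-sample test of 5% against 3.5% gives

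n = [(1.645 × √(0.05 × 0.95) + 1.282 × √(0.035 × 0.965)) / 0.015]² ≈ 1569.

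The arcsine version gives about 1537. Both are within 2% of 1544, so the stated number is reproduced on this reading. A two-sided test gives 1952, and a plain 95% interval with a half-width of 1.5 points needs 811. The loss allowance is (1600 − 1544)/1600 = 56/1600 = 3.5%.

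**2. Information left for CKD.** Day-90 loss (death plus non-attendance) is not in the article, so the rates below are assumptions. With n = 1600 × (1 − loss):

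- power = Φ[(0.015√n − 1.645√0.0475) / √0.033775]
- half-width = 1.96√(0.0475/n)

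| Assumed loss | Evaluable n | Half-width at 5% | Power, 5% vs 3.5% |
|---|---|---|---|
| 3.5% (plan) | 1544 | 1.09 points | 90% |
| 10% | 1440 | 1.13 points | 87% |
| 20% | 1280 | 1.19 points | 83% |
| 30% | 1120 | 1.28 points | 78% |
| 40% | 960 | 1.38 points | 72% |

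The half-width stays within 1.5 points until n falls to 811, a loss of 1 − 811/1600 ≈ 49%. So power falls short of the stated figure, while the stated precision survives.

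**3. Bias at the 5% boundary.** Let p be the true CKD prevalence at admission. Let f1 and f0 be the shares with a day-90 result among patients with and without CKD.

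- *(a) Denominator = attenders:* estimate = p·f1 / [p·f1 + (1 − p)·f0]. It is below 5% when f1/f0 < 0.05(1 − p)/(0.95p).
  - p = 6%: 0.047/0.057 = 0.82
  - p = 7.7%: 0.04615/0.07315 = 0.63
- *(b) Denominator = all enrolled, unconfirmed counted as non-CKD:* estimate = p·f1. It is below 5% when f1 < 0.05/p.
  - p = 6%: f1 < 0.83
  - p = 7.7%: f1 < 0.65

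Example with assumed f1 = 0.60 and f0 = 0.75, an overall loss of about 26%:

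- True 6% gives (a) 0.036/0.741 = 4.9% and (b) 3.6%.
- True 7.7% gives (a) 0.0462/0.73845 = 6.3% and (b) 4.6%.

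If f1 = f0, estimate (a) equals p and there is no bias.

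**4. Visit window.** Ten working days are about 14 calendar days, so Visit G may fall between about day 76 and day 104. The early end is short of the three months that the Limitations section requires. Early tests could count slowly recovering acute kidney injury as chronic, which would push the estimate up.

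**The case against.** Several points on the other side stand.

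- A reader might infer that no correction is planned. The Analysis section does plan chained-equation imputation where appropriate, and details may sit in an analysis plan that is not shown. What stands is narrower: the article claims confidence for CKD, admits the bias, and connects no method to it.
- A reader might infer that CKD can be known only in survivors who attend. That holds for the scheduled study test. Medical history and diagnosed chronic conditions are also recorded, so CKD documented before admission can be known in patients who die. The Introduction says that diagnosis is often delayed until emergency presentation, so the gain may be small.
- A reader might infer that the 3.5% allowance causes a wrong decision. It does not: it affects power, the 1.5-point half-width is robust, and more patients would leave the bias unchanged.
- A reader might infer that CKD will be wrongly excluded. This needs differential loss or an unfavourable denominator, and the article fixes neither. Suppose 25% die, 10% of survivors are lost, and CKD is present in 15% of those who die and 6% of survivors (all assumed). The truth is 0.25 × 15% + 0.75 × 6% = 8.25%. The attenders-only estimate is 6.0%, still above the boundary. Only confirmed cases over all enrolled, 0.75 × 0.90 × 6% = 4.05%, falls below it.
- Requiring local residence and phone contact limits loss among survivors, and early tests may bias the estimate upward. The net direction is therefore not determined.
- The authors disclose the survivorship bias openly.

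**Conclusion.** The point holds in limited form. The confidence and 90% power stated in Sample size are not delivered for CKD by a diagnosis that depends largely on day-90 attendance with a 3.5% allowance, and that section conflicts with Limitations. Under assumed loss of 20% to 30%, power is about 83% to 78%, while the stated precision holds up to about 49% loss.

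The larger risk is bias. With differential loss, a true 6% or 7.7% can be estimated below 5%: on attenders, when the relative chance of a day-90 result is below about 0.82 or 0.63, and more easily if unconfirmed patients count as non-CKD. The documents do not show that this will happen. Mortality, attendance and their relation to CKD are all assumptions here. The early edge of the Visit G window conflicts with the three-month requirement whatever those rates are.

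**What to change.** The Study status section says that follow-up is under way and analysis has not been performed, so these changes can be made before results are seen.

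1. Restate the expected evaluable number and power for CKD separately from the other conditions, over a stated range of day-90 loss, and qualify the sentence on confidence. No further enrolment is needed.
2. Apply the 5% rule to a CKD estimate for all admissions. Use the imputation already planned, or inverse-probability weighting, with admission creatinine, urine dipstick, age, HIV, hypertension, diabetes and prior CKD history. State how deaths and non-attenders are handled. Because either method assumes that these variables explain the loss, add bounds with unconfirmed patients who had low eGFR at admission counted first all as CKD and then all as non-CKD.
3. Reconcile the Visit G window with the three-month requirement. In the analysis, use the actual interval between tests and flag confirmations at shorter intervals as provisional.

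The cost is wording and modest extra analysis, since creatinine and dipstick are already scheduled at admission. The stated figure for CKD becomes less favourable, and wide bounds may show that the cohort cannot settle the question alone.
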